# Cell-free stem cell-derived extract formulation for treatment of knee osteoarthritis: study protocol for a preliminary non-randomized, open-label, multi-center feasibility and safety study

**DOI:** 10.1186/s13018-021-02672-3

**Published:** 2021-08-20

**Keywords:** Musculoskeletal injuries, Knee osteoarthritis, Regenerative medicine, Stem cells, Progenitor cells, Growth factors, Cytokines, Extracellular vesicles, Exosomes, Clinical trial

## Abstract

**Background:**

Musculoskeletal conditions are highly prevalent, and knee OA is most common. Current treatment modalities have limitations and either fail to solve the underlying pathophysiology or are highly invasive. To address these limitations, attention has focused on the use of biologics. The efficacy of these devices is attributed to presence of growth factors (GFs), cytokines (CKs), and extracellular vesicles (EVs). With this in mind, we formulated a novel cell-free stem cell-derived extract (CCM) from human progenitor endothelial stem cells (hPESCs). A preliminary study demonstrated the presence of essential components of regenerative medicine, namely GFs, CKs, and EVs, including exosomes, in CCM. The proposed study aims to evaluate the safety and efficacy of intraarticular injection of the novel cell-free stem cell-derived extract (CCM) for the treatment of knee OA.

**Methods and analysis:**

This is a non-randomized, open-label, multi-center, prospective study in which the safety and efficacy of intraarticular CCM in patients suffering from grade II/III knee OA will be evaluated. Up to 20 patients with grade II/III OA who meet the inclusion and exclusion criteria will be consented and screened to recruit 12 patients to receive treatment. The study will be conducted at up to 2 sites within the USA, and the 12 participants will be followed for 24 months. The study participants will be monitored for adverse reactions and assessed using Numeric Pain Rating Scale (NPRS), Patient-Reported Outcomes Measurement Information System (PROMIS) Score, Knee Injury and Osteoarthritis Outcome Score Jr. (KOOS Jr.), 36-ietm short form survey (SF-36), Single Assessment Numeric Evaluation (SANE), physical exams, plain radiography, and magnetic resonance imaging (MRI) with Magnetic Resonance Observation of Cartilage Repair Tissue (MOCART) score for improvements in pain, function, satisfaction, and cartilage regeneration.

**Discussion:**

This prospective study will provide valuable information into the safety and efficacy of intraarticular administration of cell-free stem cell-derived extract (CCM) in patients suffering with grade II/III knee OA. The outcomes from this initial study of novel CCM will lay the foundation for a larger randomized, placebo-controlled, multi-center clinical trial of intraarticular CCM for symptomatic knee OA.

**Trial registration:**

Registered on July 21, 2021. ClinicalTrials.gov NCT04971798

## Background

Osteoarthritis (OA) and other orthopedic acute and degenerative conditions affect millions of people each year, resulting in marked pain and disability [1–3]. Knee OA is the most prevalent and is estimated to affect 67 million people by the year 2030 [4]. Conservative modalities are limited, as they do not reverse the underlying pathology and may only provide symptomatic relief [3–11].

To address the limitations of traditional conservative modalities, there has been substantial interest in biologics for musculoskeletal regenerative medicine applications [6, 12]. The efficacy of biological products is attributed to the presence of growth factors (GFs), cytokines (CKs), and extracellular vesicles (EVs) including exosomes [13–16].

First-generation biologics, specifically whole stem cell products, are not without limitations, including establishing a reliable source with a stable phenotype, genetic instability and chromosomal aberrations, intravenous administration-related toxicities caused by the physical trapping of the cells in the lung microvasculature, rejection by the host, formation of ectopic tissue, and tumorigenicity [17–20].

When considering how to harness the value of current biologics into a next generation product that can address existing limitations, it is important to consider the current knowledge regarding the mechanism of action of stem cell products. The recent literature regarding the beneficial effects of mesenchymal stem cells (MSCs) postulates that the mechanism of action does not result from their ability to grow and differentiate. Rather, it is secondary to their secretion of bioactive molecules such as GFs, CKs, and exosomes [21–24]. GFs, secreted from stem cells, induce signal transduction pathways that initiate cell migration, proliferation, growth, and differentiation [25]. CKs, similarly, can regulate inflammation, immune response, cellular differentiation, and tissue remodeling [26]. Exosomes also are secreted by mesenchymal stem cells and act as a paracrine mediator to target cells, providing a regenerative microenvironment for damaged tissues [23, 27, 28].

As the existing literature establishes that these components of stem cells produce definite regenerative responses, we have accordingly sought to establish whether a sub-cellular approach to biologics can provide similar benefits while avoiding the risk profile, including immunogenicity, infection, and the potential for tumorigenicity, associated with whole stem cell products. Supporting this hypothesis, recent studies have demonstrated that MSCs-derived exosomes can act as a cell-free therapeutic alternative to whole cell therapy with great regenerative potential [29–31]. In addition to the benefits by means of risk elimination, there may be further therapeutic benefits of a cellular derived therapeutic approach. For example, exosomes, given their smaller size, have the potential to migrate to target organs efficiently, without getting trapped in the lung microvasculature [32, 33]. Additionally, a higher concentration of “active ingredients” can be administered directly to the patient, which may induce a greater healing response than possible with whole stem cell therapies.

To meet these goals of improving the risk profile and therapeutic benefit of regenerative medicine, we have formulated a novel cell-free stem cell-derived extract (CCM) from human progenitor endothelial stem cells (hPESCs). Our preliminary results demonstrated the presence of several GFs, anti-inflammatory CKs and EVs including exosomes in this formulation [34]. Functionally, this formulation also significantly enhanced cell proliferation and induced stem cell migration [34].

The goal of this proposed study is to evaluate the safety and efficacy of intraarticular injection of this cell-free stem cell-derived extract formulation for the management of knee OA. We hypothesize that intraarticular administration of this cell-free stem cell-derived extract formulation is safe. We also hypothesize that patients receiving intraarticular injection of this formulation will show an improvement in their overall satisfaction, Numeric Pain Rating Scale (NPRS), Patient-Reported Outcomes Measurement Information System (PROMIS) score, and Knee Injury and Osteoarthritis Outcome Score (KOOS Jr.) over a period of 2 years compared to baseline. We wish to test the null hypothesis that there is no difference between baseline and follow-up visits for the outcome measures considered.

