### Study design

Up to 20 patients with grade II/III OA who meet the inclusion and exclusion criteria will be consented and screened to allow for approximately 12 patients to receive treatment for this non-randomized, open-label, multi-center, prospective study. This study will be conducted at two sites within the USA, and the participants will be followed for 24 months after the intervention. Figure 1 summarizes the trial design, and Fig. 2 illustrates the enrolment, intervention, and assessment according to the SPIRIT guidelines.

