#### Secondary endpoints

To assess the changes if any in patient-reported outcome measures, NPRS, PROMIS, and KOOS Jr., from baseline to different follow-up time points.To assess cartilage formation via MOCART at 2 years time point and compare it from baseline.To assess patient satisfaction.

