### Sample size and statistical analysis

Descriptive statistics will be computed for all study variables. Continuous variables will be described with measures of central tendency (mean, median) and dispersion (range, standard deviation). Categorical variables will be summarized as frequencies and percentages. Comparisons between categorical variables will be compared with the chi-Square test; continuous variables will be compared with Student’s *t* test or nonparametric equivalents. Paired continuous data will be assessed with a paired *t* test or Wilcoxon signed rank test, depending on distribution. Paired categorical data will be assessed with the McNemar’s test. For the longitudinal data, a mixed model repeated measures analysis will be used to examine the between subject factors and the within subject factor of time (baseline, visit 1, visit 2, etc.), as well as their interaction, on the outcome variables of interest. Post hoc tests with corrections for multiple comparisons will be run to determine where significance lies. *P* values < 0.05 will be considered statically significant.

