## Discussion

OA is one of the most common musculoskeletal conditions in the USA, affecting several joints and leading to pain, loss of function, and a decrease in quality of life [37]. This also leads to a substantial burden on the healthcare system [38]. The knee is the most frequently affected joint, and current efforts to mitigate knee OA are focused on decreasing pain, increasing function, and improving quality of life [38]. These current treatment options have limitations, as symptomatic treatment fails to address the underlying pathophysiological processes associated with OA or regenerate injured cartilage [38]. This is one of the several reasons why the field of regenerative medicine and interest in the use of biologics, including cell-free biologics, has increased so rapidly [27, 34, 37].

This clinical trial will be the first to evaluate the safety and efficacy of intraarticular cell-free stem cell-derived extract (CCM) in patients with Kellgren grade II or III knee OA. We anticipate that the intraarticular injection of CCM is safe, and participants will show an improvement in their pain, function, quality of life, and overall satisfaction. We also hypothesize that the cartilage formation over a period of 2 years compared to the baseline visit will improve. The positive outcomes from this trial will also lay the foundation for a large randomized, placebo-controlled, multi-center trial of intraarticular CCM for symptomatic knee OA.

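### Efficacy is an aim, but the only stated test is zero change from baseline in one open-label group, which an inert injection could also pass

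*Protocol article*

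**What the plan says.** - **Aim** (Background): "The goal of this proposed study is to evaluate the safety and efficacy of intraarticular injection of this cell-free stem cell-derived extract formulation". The Abstract and the Discussion also pair safety with efficacy.
- **Hypothesis** (Background): the patient-reported scores and satisfaction are expected to improve relative to baseline over two years, and the test is "We wish to test the null hypothesis that there is no difference between baseline and follow-up visits for the outcome measures considered".
- **Design** (Abstract, Methods and analysis): "This is a non-randomized, open-label, multi-center, prospective study in which the safety and efficacy of intraarticular CCM". Study design gives the size: "consented and screened to allow for approximately 12 patients to receive treatment". There is one treated group and no comparator.
- **Endpoints**: the primary endpoint is safety. The first secondary endpoint is "To assess the changes if any in patient-reported outcome measures, NPRS, PROMIS, and KOOS Jr., from baseline to different follow-up time points"; the others are MOCART at two years against baseline, and satisfaction.
- **Analysis** (Sample size and statistical analysis): paired t or signed-rank tests for paired data, a repeated-measures mixed model for longitudinal data, post hoc tests corrected for multiple comparisons, and "values < 0.05 will be considered statically significant".
- **Entry rules**: Inclusion criteria require an average knee pain of at least 6 on the NPRS. Exclusion criteria rule out pain medication in the 15 days before injection.
- **Use of the result** (Discussion): "The positive outcomes from this trial will also lay the foundation for a large randomized, placebo-controlled, multi-center trial".
- **Title**: "study protocol for a preliminary non-randomized, open-label, multi-center feasibility and safety study".

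**The concern.** A test against zero change answers whether scores moved, not whether the product moved them. In a single open-label group the two questions separate, because several things other than the product can move the scores:

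- Patients are selected for a high value on NPRS, which is then tested as an outcome, so regression to the mean is built in.
- Stopping pain medication before the injection may raise the starting value.
- Patients know that they received the product, and most outcomes are their own ratings.

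No control group, external benchmark, minimum change or expected placebo response is named against which a change could be read. The efficacy aim therefore rests on a null hypothesis that could be false for reasons unrelated to the product. At stake is a published statement about efficacy that the design cannot support, cited as the groundwork for a larger trial.

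A smaller mismatch sits alongside: the title announces feasibility, but neither the primary nor the secondary endpoints include a feasibility measure.

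**Working it through.** The article gives no power, effect size, SD or derivation of the sample size, so there is no figure of its own to reproduce.

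**Inputs from the article.** n = 12 treated; significance at 0.05 (sidedness not stated, two-sided used here); paired t test; entry at NPRS ≥ 6. Assessment points places NPRS after injection at visits 2.2, 3, 4 and 5 to 11: 3 + 7 = 10 visits.

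**Assumed inputs.** SD of NPRS change 2 to 2.5; non-specific mean drop of 1, 1.5 or 2 points with no product effect.

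**Step 1. One uncorrected paired t test.** The rejection probability is that of a noncentral t with 11 degrees of freedom and noncentrality δ = (drop / SD) × √12. The two-sided 0.05 critical value is 2.201.

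| Drop | δ, SD 2 | Rejects | δ, SD 2.5 | Rejects |
|---|---|---|---|---|
| 0 | 0 | 0.050 | 0 | 0.050 |
| 1 | 1.732 | 0.353 | 1.386 | 0.245 |
| 1.5 | 2.598 | 0.658 | 2.078 | 0.475 |
| 2 | 3.464 | 0.883 | 2.771 | 0.714 |

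The test keeps its 5% level only if the true mean change is exactly zero.

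**Step 2. With a multiplicity correction.** The article promises correction of post hoc tests but names no method. With Bonferroni over the 10 NPRS visits (assumed), each test uses 0.05 / 10 = 0.005 and the critical value is 3.497.

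| Drop | SD 2 | SD 2.5 |
|---|---|---|
| 1 | 0.086 | 0.049 |
| 1.5 | 0.256 | 0.140 |
| 2 | 0.518 | 0.303 |

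These are probabilities per visit. They are much lower than in step 1, but 0.049 is still about ten times the nominal 0.005 (0.049 / 0.005 = 9.8).

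**Step 3. Regression to the mean alone.** Assume that NPRS in the screened population is normal with mean μ of 5 to 6, SD σ of 1.5 to 2 and test-retest correlation ρ of 0.5 to 0.8, with no placebo or product effect. Selecting at ≥ 6 gives an expected drop of (1 − ρ) × σ × φ(z) / [1 − Φ(z)], where z = (6 − μ) / σ.

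- Smallest: μ = 6, σ = 1.5, ρ = 0.8. Then z = 0, the ratio is 0.798, and the drop is 0.2 × 1.5 × 0.798 = 0.24.
- Largest: μ = 5, σ = 2, ρ = 0.5. Then z = 0.5, the ratio is 1.141, and the drop is 0.5 × 2 × 1.141 = 1.14.

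In simulated trials of 12 across these ranges, an uncorrected paired t test showed significant improvement with probability from 0.13 to about 0.60, against 0.025 nominal in that direction. The model ignores the 0-10 bounds of the scale and takes the entry value as the baseline. If entry rests on a pain average, the correlation is higher and the effect smaller.

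**Step 4. Title against endpoints.** The title names feasibility and safety. The endpoint sections list safety, patient-reported change, MOCART and satisfaction. The word feasibility does not recur in the text.

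**The case against.** The other side has real substance.

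- **No decision rule is stated.** A reader might infer that a significant change will be declared as efficacy and will trigger the randomized trial. The article does not say so. The secondary endpoint is worded as changes if any, the hypothesis is improvement against baseline rather than placebo, the Abstract refers neutrally to the outcomes, and the phrase about positive outcomes is one sentence of Discussion. This stands. What remains is that efficacy is an aim and the baseline null is the only test offered for it.
- **The limits are visible.** The study is labelled preliminary, safety is the sole primary endpoint, and the next step foreseen is placebo-controlled. An uncontrolled early study is acceptable. This lowers the severity, but does not make the efficacy wording right.
- **The figures rest on assumptions.** No SD, placebo response or correlation is given, and longitudinal data go to a mixed model with corrected contrasts rather than to single t tests. This stands: the direction holds across the ranges, the size does not.
- **Multiplicity.** A reader might also infer a large false-positive rate from the number of outcomes and visits. The text does not support a figure, because correction is promised, its scope is not stated, and repeated scores in the same patients are correlated.
- **Not every outcome is self-reported.** MOCART is read from MRI, so expectation bears on it less. It still has no comparator.
- **Medication.** Patients must also be willing to forgo symptom-modifying drugs to the end of the study, so the pre-injection restriction need not produce a later fall in pain. It is a possible contributor only.
- **Feasibility.** It would be too strong to say that the study will show nothing about feasibility: screening, retention and completion data arise anyway, and progression thresholds may sit in the full protocol. What stands is that the article's title and its own endpoint list disagree.

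**Conclusion.** The point holds at should-fix level. The article pairs an efficacy aim with a null hypothesis that a product with no effect could lead the trial to reject. For an assumed non-specific NPRS drop of 1 to 2 points and SD of change 2 to 2.5, one uncorrected test at n = 12 rejects in about 25% to 88% of trials. With Bonferroni over 10 visits the range is about 5% to 52% per visit. Regression to the mean alone gives about 13% to 60% uncorrected under the assumptions of step 3. The supported conclusion is that the test *could* be passed without a product effect, not that it would be. The primary safety endpoint is unaffected. The mismatch between the title and the endpoints is real but secondary.

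**What to change.** **1. Hypothesis and aims.** Replace the null-hypothesis sentence in the Background with wording such as:

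> Secondary outcomes will be reported as within-patient change from baseline with 95% confidence intervals. P values are descriptive. Because there is no control group, no conclusion on efficacy will be drawn.

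Change *efficacy* to *change from baseline* in the Abstract, the aims and the Discussion, and carry the same statement into the analysis section.

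**2. Feasibility.** Either drop the word from the title, or list measures that the study already generates: number screened per patient treated, retention, completion of NPRS and MRI, and the SD of NPRS change with its confidence interval. Their precision should be stated. If 12 of 20 screened are treated, the proportion is 60% with an exact 95% interval of 36% to 81%. With 11 degrees of freedom, the 95% limits for an SD are √(11 / 21.92) = 0.71 and √(11 / 3.816) = 1.70 times the estimate.

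**Cost.** Edits to wording and a few summaries of data already collected; no extra patients or visits. The price is that this study can make no efficacy claim.

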## Methods and analysis

The Standard Protocol Item-Recommendations for Intervention Trials (SPIRIT) criteria were used to report this study protocol [35]. The complete SPIRIT checklist can be found within the supplementary data.

### Study design

Up to 20 patients with grade II/III OA who meet the inclusion and exclusion criteria will be consented and screened to allow for approximately 12 patients to receive treatment for this non-randomized, open-label, multi-center, prospective study. This study will be conducted at two sites within the USA, and the participants will be followed for 24 months after the intervention. Figure 1 summarizes the trial design, and Fig. 2 illustrates the enrolment, intervention, and assessment according to the SPIRIT guidelines.

**Fig. 1 Fig1:**
[figure not shown]
Summary of trial design

**Fig. 2 Fig2:**
[figure not shown]
Standard protocol items: recommendations for interventional trials (SPIRIT) flowchart

#### Inclusion criteria

Patients will be considered for inclusion in the study if they meet the following criteria:
18 years of age or olderBMI of ≤ 35Kg/m^2^Willing and capable of providing informed written consentWilling and capable of subjective evaluation and able to understand written questionnairesDiagnosed with mild to moderate knee OA in only one knee with a grade II/III on the Kellgren Lawrence (KL) grading scaleAverage knee pain intensity of ≥ 6 on the NPRSWilling to not take any knee symptom modifying drugs through the end of the studyWilling and able to comply with study-related requirements, procedures, and visitsIf female, sexually active, and of childbearing age, patients must be willing to use a reliable form of birth control throughout the duration of the study. If male, sexually active, and with partners of childbearing age, patients must be willing to use contraceptive measures.

#### Exclusion criteria

In addition to the inclusion criteria, patients must not meet any of the following exclusion criteria:
Taken any pain medications, including NSAIDS, within 15 days prior to the study injection date.Use of anticoagulants or history of the regular use of anticoagulantsHistory of addiction to dependency producing medications or substance abuse, including alcohol or illicit drugsMechanical knee symptoms consistent with extensive intraarticular pathology not amenable to injection therapy alone, including clinical or imaging evidence of anterior cruciate ligament, posterior cruciate ligament, medial collateral ligament, lateral collateral ligament, or meniscal pathologyUndergone an intraarticular injection of any drug or device including but not limited to corticosteroid, platelet rich plasma or viscosupplementation in the index knee within the last 3 monthsHistory of any type of surgery in the index kneeRecent (within 3 months) history of traumatic injuryPlanned elective knee surgery during the duration of the studyHistory of organ or hematologic transplantationHistory of rheumatoid arthritis or other autoimmune disordersHistory of immunosuppressive medication/treatment or cancer diagnosis within the last 5 yearsCurrent knee infection or history of using antibiotics for a knee infection within the last 3 monthsParticipation within another clinical study or received treatment with any investigational product within 30 days of enrollmentCurrently pregnant, as determined by urine testingBreastfeeding, or desires pregnancy during the course of the studyContraindications to plain radiography or MRI imagingDiagnosis of progressive neurological diseaseDiagnosis of an active psychological or psychiatric disorderPain within other areas and/or medical conditions that could interfere with pain reporting, study procedures, and/or confound evaluation of the studyUnresolved major issues of secondary gain (e.g., social, financial, or legal)

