### Study intervention

After the patients have meet all inclusion/exclusion criteria during visit 1 (preliminary/baseline), they will receive an intraarticular injection of CCM (2 ml, General Therapeutics LLC, Cleveland Heights, OH, USA) formulation via anterolateral approach by the site principal investigator (PI) utilizing ultrasound guidance per PI’s standard institutional protocol during visit 2.1 (injection visit/procedure).

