### Assessment points

The assessments for the study period will begin at visit 1 (preliminary/baseline), where patients will be screened for the inclusion/exclusion criteria and asked to sign the informed consent form. Once enrolled, the demographic information, medical history, medication history, and vitals will be collected. A baseline physical exam (PE) that includes knee ligament laxity and active/passive range of motion evaluation will be performed. Baseline plain radiography (weight bearing anteroposterior, lateral with 30° of knee flexion, Merchant and Rosenberg views) and MRI imaging (including T2 imaging and institutional standard protocol) will be performed for OA grading using the KL scale and Magnetic Resonance Observation of Cartilage repair Tissue (MOCART) score, respectively. Baseline case report forms (CRFs) including NPRS, KOOS Jr., PROMIS, Neuro-QoL Short Form v1.0, Lower extremity function-Mobility, PROMIS Short Form V2.0 - Physical Function 10a and 10b, and patient satisfaction/survey (SF-36 and Single assessment Numeric Evaluation (SANE)) will be collected. Additionally, a comprehensive metabolic profile (CMP), creatinine (Cr), erythrocyte sedimentation rate (ESR), T, B, and NK cell lymphocytes subsets, and serum IgG, IgA, IgM, and IgE levels will be collected. The vitals will be recorded followed by administration of injection by the site PI on visit 2.1. During visit 2.2 (immediately after injection follow-up + 15 min after injection), the vitals and NPRS will be recorded. Visits 3 (24 h follow-up ± 2 h) and 4 (48 h follow-up ±2 h) will be completed via phone interview, and NPRS will be collected. On visit 5 (1 week follow-up ±1 day), a PE will be performed and specific CRFs (NPRS, KOOS Jr., PROMIS, 5 point Likert scale and SANE) as well as a comprehensive metabolic profile (CMP), creatinine (Cr), erythrocyte sedimentation rate (ESR), T, B, and NK cell lymphocytes subsets, and serum IgG, IgA, IgM, and IgE levels will be collected. The exact same process will take place through visits 6 (6 week follow-up ± 3 days), 7 (3 month follow-up ± 7 days), and 8 (6 month follow-up ± 14 days) with a plain radiograph at each visit. SF-36 will also be collected at visits 7 and 8. At visit 9 (12 month follow-up ± 21 days), the participants will undergo the aforementioned processes with an MRI for MOCART grading. At visit 10 (18 month follow-up ± 28 days), the participants will undergo a PE, plain radiography, and CRFs (NPRS, KOOS Jr., PROMIS, 5 point Likert Scale, SANE and SF-36). At visit 11 (24 month follow-up ± 28 days), the participants will undergo the aforesaid processes with an MRI for MOCART grading. An empirical grading form evaluating six distinct articular elements namely, cartilage, osteophytes, subchondral sclerosis, bone marrow lesions, joint effusion, and synovitis, involved in the pathoanatomy of knee osteoarthritis using MRI will also be evaluated at baseline and at 12- and 24-month follow-up visits [36]. Participants may report any adverse events or changes in medications at any point during the study. Unscheduled visits may occur at any time for possible study-related adverse events.

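### The 15-day analgesic washout is dated to the injection but the baseline questionnaires are taken at visit 1, so any gap between the visits leaves the baseline only partly protected

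*Protocol article*

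**What the plan says.** All references are to the protocol article.

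- **Washout.** The Exclusion criteria rule out a patient who has "Taken any pain medications, including NSAIDS, within 15 days prior to the study injection date". The clock runs back from the injection.
- **Eligibility check.** Study intervention states: "After the patients have meet all inclusion/exclusion criteria during visit 1 (preliminary/baseline), they will receive an intraarticular injection of CCM". The injection itself is at visit 2.1.
- **Visit 1.** Assessment points describes it as the visit "where patients will be screened for the inclusion/exclusion criteria and asked to sign the informed consent form". It continues: "Once enrolled, the demographic information, medical history, medication history, and vitals will be collected". The same visit supplies "Baseline case report forms (CRFs) including NPRS, KOOS Jr., PROMIS, Neuro-QoL Short Form v1.0", together with SF-36 and SANE.
- **Visit 2.1.** The only assessment listed before the needle is in this sentence: "The vitals will be recorded followed by administration of injection by the site PI on visit 2.1". The next NPRS is at visit 2.2, after the injection.
- **After entry.** The Inclusion criteria ask for willingness to stay off drugs that modify knee symptoms until the study ends. This rule looks forward only.
- **Use of the baseline.** The first secondary endpoint is change in NPRS, PROMIS and KOOS Jr. from baseline. Patient satisfaction is also a secondary endpoint. There is no control arm.

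**The concern.** A washout should be complete when the outcome it protects is measured. Here it is tied to a later event. Suppose a patient is taking an NSAID at visit 1, stops, and is injected 15 or more days later. That patient satisfies the exclusion as written, yet gave the baseline NPRS, KOOS Jr. and PROMIS on the drug. With a shorter gap, the baseline could be partly washed out.

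Follow-up is meant to be free of symptom-modifying drugs, so for such a patient the change from baseline would mix any effect of the product with the effect of stopping analgesics. If analgesics had lowered the visit 1 pain score, improvement would be understated. No comparison group exists to separate the two effects. The medication history at visit 1 could identify these patients, but it cannot supply an off-drug score that was never taken.

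**Working it through.** The article gives no effect size, standard deviation or power for its 12 patients, so there is no planned figure to reproduce. The check is date arithmetic.

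**Inputs**
- Washout: 15 days before injection (Exclusion criteria).
- Baseline questionnaires: visit 1 (Assessment points).
- g, the days from visit 1 to injection: not in the text shown; assumed range 0 to 30.

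**Formula.** Drug-free days guaranteed at baseline = max(0, 15 - g).

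| g (days, assumed) | Guaranteed drug-free days at baseline |
|---|---|
| 0 | 15 |
| 1 | 14 |
| 3 | 12 |
| 7 | 8 |
| 10 | 5 |
| 14 | 1 |
| 15 to 30 | 0 |

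Only same-day visits secure all 15 days. For gaps of 1 to 14 days the wording permits a partly washed-out baseline. From 15 days on it permits a baseline taken on the drug.

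**What this could do to the mean.** If k of the 12 patients are affected and stopping analgesics raises NPRS by d points, the mean change shifts by k × d / 12. Both k and d are assumptions, so the values below only show how the shift scales:
- k = 1, d = 0.5 to 1.5: 0.5/12 = 0.04 to 1.5/12 = 0.13 points.
- k = 3, d = 1.0: 3/12 = 0.25 points.
- k = 6, d = 1.0: 6/12 = 0.50 points.
- k = 12, d = 1.5: 18/12 = 1.5 points, the top of the assumed range.
- k = 0, or g = 0: no shift.

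**After the change.** With the questionnaires at visit 2.1, or with the 15 days counted back from visit 1 and maintained, the guarantee is at least 15 days for every g.

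**The case against.** The strongest counter-argument comes from the article itself. Study intervention has all criteria met during visit 1, and Assessment points places screening and consent before enrolment and lists the baseline forms after it. Read strictly, a patient completes the questionnaires only when already off medication. This stands in part: it makes an on-drug baseline less likely. It does not settle the matter, because the criterion still refers to the injection date and a condition dated to a later event cannot be finally confirmed at an earlier visit. Two sites could apply it differently.

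Second, the interval and the visit grid may be in Fig. 1 or Fig. 2, which are not shown, or in the full protocol. This stands. A reader might infer that the plan fails to define the interval, but the documents do not support that. The point is that two stated rules use different dates.

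Third, a reader might infer that the visits must be apart because visit 1 imaging decides eligibility: the exclusions mention pathology "including clinical or imaging evidence of anterior cruciate ligament" and other structures. The text does not establish this. It describes the visit 1 imaging after enrolment, pairs radiography with KL grading and MRI with MOCART, and does not say that the imaging evidence must come from the visit 1 scans. Numbering same-occasion steps 2.1 and 2.2, with a separate visit 1, suggests different occasions but does not prove it.

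Finally, only secondary outcomes are touched, probably in the conservative direction, in a small feasibility study. This also stands and keeps the severity low.

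**Conclusion.** The washout and the baseline measurement are fixed to different dates, so the wording guarantees max(0, 15 - g) drug-free days at baseline, not 15. The consequence is conditional. It needs visit 1 and visit 2.1 to fall on different days, and at least one patient to have used analgesics near visit 1. If both hold, that patient's change from baseline would probably understate improvement, assuming analgesics lowered the visit 1 pain score and follow-up was drug-free.

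The size of any bias cannot be derived from the document, and the NPRS shifts shown are illustrations on assumed values. A reader might infer that the efficacy baseline is contaminated, that power is lost, or that false evidence of benefit would follow. None of these is supported: the gap and analgesic use at visit 1 are unknown, no power target is stated, and the likely direction is against the product. The primary safety endpoint is not affected. This is a low-severity improvement, worth making because it is cheap and works whatever the gap.

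**What to change.** Either of two changes is enough.

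1. **Move the baseline.** Collect NPRS, KOOS Jr., PROMIS, SANE and SF-36 at visit 2.1 before the injection, once the 15-day washout is confirmed. Name these scores as the baseline for the secondary endpoints and for the baseline level of the time factor under Sample size and statistical analysis, where baseline and visit 1 are now listed separately. Keep the NPRS entry threshold of 6 at visit 1. Reword Study intervention so that eligibility is screened at visit 1 and the washout is confirmed at visit 2.1. SANE and SF-36 must be included, because otherwise the satisfaction and survey forms would keep the visit 1 baseline.
2. **Move the washout.** Require 15 drug-free days to be complete before the visit 1 questionnaires and maintained until injection.

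The first option costs one repeat set of short questionnaires at an existing visit. The two pre-injection scores may differ, and some patients may score below 6 at visit 2.1, so the text must say that eligibility rests on visit 1 and change is measured from visit 2.1. The second needs no extra forms but lengthens the drug-free period before injection from 15 to 15 + g days.
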